#### Provider level

Physicians in the intervention arm will receive summary reports of their patients’ adherence to their medications and BP data tailored by them (e.g., average and range of SBP/DBP readings, percent of SBP/DBP controlled, and so forth) every 2 weeks using only patient ID numbers. They will also receive summary charts of expert consensus BP management guidelines used in other studies [47]. If a patient’s mean BP exceeds the thresholds, the PINGS nurse navigator will call the patient and conduct the BP protocol again, and initiate a follow-up action as needed. The nurse navigator will also contact those patients who show medication adherence below .80 and/or whose monthly MPRs do not reflect the information in the self-reported medication intake summary reports. They will use motivational interviewing to help the patient to eliminate the barriers related to poor medical regimen adherence.

### Control arm/standard of care

Inclusion criteria include owning a cell phone with at least SMS and voice mail. To control for attention exposure, they will receive SMS messages dealing with healthy lifestyle behaviors (smoking, diet, physical activity) but not with medication adherence, hypertension- or stroke-related issues. Messages will be of the same frequency and size as those in the intervention arm. Every 3 days (comparable to those in the intervention arm) they will receive lifestyle messages and if they have a smartphone, the SMS messages will have either PDFs attached or weblinks to a brief video clip or series of charts, information, and so forth. This information will be sent in two messages and requires 3–5 min per message to view or listen to (similar to the BP protocol duration). All four physicians will receive the expert consensus guideline charts. Intervention tactics will cease for both groups after the 3-month trial.

### Follow-up phase

Subjects in both arms of the study will be followed up for 6 months after the initial 3-month trial. During the follow-up period, subjects will attend clinics monthly where their physicians will assess them clinically. At months 3, 6 and 9 post enrollment patients and providers will undergo assessments on methodological parameters and consumer responses, clinic BP measurements, medication adherence, health literacy on stroke and HTN as well as self-determination theory constructs such as Autonomous Self-regulation and Competence Scales. Physicians in both groups will also undergo assessment on adherence to BP management protocols (Fig. 1 and Table 1).

**Table 1 Tab1:** Study outcome measures

Outcomes	Psychometrics (internal consistency [α], test-retest reliability [r]) NOTE A^a^	Time points
Primary outcomes		
Feasibility: methodological parameters and consumer responses	Recruitment and retention rates; Self-report: Patient/Provider Satisfaction Scale (.82–.96, test-retest (1 week) .98) [74, 75], fidelity checklists: patient level (e.g., connection; BP uploads via phone; opening of messages/educational information and provider level (e.g., delivery of provider summaries; phone alerts)	Baseline, 3, 6, 9 months
Clinic: BP	Clinic-based BP	
Feedback and refinement	Focus groups	Providers and IG: 9 months
Secondary outcomes		
Medication adherence Physician adherence	Medication Possession Ratio (MPR); Morisky Medication Adherence Scale (α = .76–.83, r = .64) [76, 77], provider guideline adherence: timely med changes (date of script changes following BP feedback (bi-monthly PINGS reports/clinic BPs)	Baseline, 3, 6, 9 months
Self-determination theory constructs	Autonomous Self-Regulation (α = .81–.84, r = .38) [78], Competence Scale (α = .88–.95, r = .32–.46) [51, 52, 78].	
Potential moderators/mediators		
Demographics	Age, education level, income	Baseline
HTN/stroke knowledge, health literacy, anthropometrics	Self-report: HTN/stroke knowledge (.70) [54, 55], health literacy (r = .74, .82) [78–80], Height/ weight/girth	Baseline, 3, 6, 9 months
Medication adherence factors	Side effects, adverse events	As reported, and 3, 6, 9 months

^a^Basic psychometric property analyses (e.g., internal consistency, test-retest reliability) will be conducted during first 3 months on scales, which have not been used with Ghanaian stroke patients

*BP* blood pressure, *HTN* hypertension, *IG* Intervention Group

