#### Secondary outcome measures

These will include outcomes such as MPR, Morisky Medication Adherence Scale (MMAS) score and Competence and Autonomous Self-regulation Scale scores.

Table 1 shows all outcome variables, questionnaires to be used and when they will be administered. We will assess self determination theory-related constructs of competence [48, 49], and autonomous self-regulation [50, 51]. We will also assess HTN knowledge [52, 53], medication side effects, stroke knowledge, self-reported medication adherence (MMAS), beliefs and life goals [54, 55] and MPR [56].

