#### Recruitment

A list of eligible patients will be identified from hospital medical records by a research assistant (RA) with the identity of the patients’ doctors not included. The research coordinator (RC) will contact and schedule eligible patients for screening/recruitment and obtain informed consent voluntarily from patients who are interested in the study. Subjects whose SBP averages ≥140 mmHg from the last two readings of the 10-min protocol will have their height, weight and waist circumference measured. A set of questionnaires will be administered to assess study outcome measures (see Table 1). The study site admits an average of 43 stroke patients each month. Based upon the stroke with HTN incidence patterns in the KATH and SMASH pilot work [38–40, 47], we will recruit eight patients (four intervention group patients and four control group patients) per month for enrollment into the study.

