### Statistical analyses

#### Feasibility outcomes

We will use 95 % confidence intervals (CIs) for proportions to estimate dichotomous outcomes (e.g., proportion agreeing to participate); adherence to protocol (e.g., use of a medication pill tray, use of a smartphone to send BP measurements, opening of SMS/voice mail messages, and so forth). Frequency distributions will be developed describing reasons for provider and patient protocol nonadherence, dropout and problems encountered such as technology glitches, medication side effects, and so forth. For continuous measures (e.g., patient satisfaction scores), frequency distributions and median and mean responses (with 95 % CIs) will be used. Chi-square tests (categorical measures) and pooled *t* tests (or Wilcoxon rank sum tests) for continuous measures will compare intervention group and SC groups.

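### Table 1 lists side effects as a potential moderator/mediator but schedules no baseline assessment, so symptoms present at entry cannot be separated from new ones

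*Protocol article*

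**What the plan says.** Table 1, under Follow-up phase, has a block headed "Potential moderators/mediators". One row of that block, on medication adherence factors, contains "Side effects, adverse events" with the time points "As reported, and 3, 6, 9 months". The row on knowledge, health literacy and anthropometrics in the same block reads "Baseline, 3, 6, 9 months", and so does the secondary-outcome row with the Medication Possession Ratio and the Morisky scale.

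Three other places bear on the point:

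- **Outcome measures, Secondary outcome measures** names side effects but gives no time: "We will also assess HTN knowledge [52, 53], medication side effects, stroke knowledge, self-reported medication adherence (MMAS".
- **Recruitment** describes the baseline session by pointing back to the table: "A set of questionnaires will be administered to assess study outcome measures (see Table 1".
- **Statistical analyses, Feasibility outcomes** tabulates "dropout and problems encountered such as technology glitches, medication side effects, and so forth".

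Statistical analyses, Primary outcome measures, adds that differences between groups in ancillary moderator and mediator measures will be estimated with 95% confidence intervals. It does not name side effects there.

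**The concern.** A moderator has to be known before the intervention acts, and a mediator is normally read as a change from a starting level. Table 1 gives side effects neither. Their first scheduled measurement comes at month 3, when, according to Control arm/standard of care, the intervention stops in both groups.

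The population makes this more than a formality. Everyone enters within one month of a stroke. Uncontrolled systolic pressure must have been recorded at an encounter before the stroke, and adherence is measured at baseline, so many patients are probably on medication at entry. Complaints such as dizziness, fatigue or headache could come from the stroke or from drugs already being taken. At stake are the interpretation of the side-effect frequencies and any exploratory use of side effects to explain adherence.

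**Working it through.** The protocol gives no figure for side effects, so there is nothing to reproduce. The check is a comparison of schedules, followed by an illustration of size.

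**Schedule in Table 1**

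| Item | Baseline | Months 3, 6, 9 | Other |
|---|---|---|---|
| Medication adherence (MPR, Morisky) | yes | yes | – |
| Knowledge, health literacy, anthropometrics | yes | yes | – |
| Side effects, adverse events | no | yes | as reported |

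**Does another section supply a baseline value?** No. Secondary outcome measures gives no time, and Recruitment defers to Table 1. The Blinding section mentions a pre-intervention evaluation but does not say that side effects are part of it. The gap is therefore a stated schedule and not a detail left open.

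**Does spontaneous reporting fill it?** Events can be recorded between enrolment and month 3. That is not a systematic question put to every patient, and the opportunity to report may differ by arm. Under Provider level, the nurse navigator calls intervention patients with low adherence or high pressure. No such call is described for controls during the 3 months, and the monthly clinics are described for the follow-up period after them.

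**Size, on assumed rates.** The protocol gives 30 patients per group. Assume that a share p = 0.30 have such symptoms at entry and that half of these persist to month 3.

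- Month-3 prevalence that is pre-existing: 0.30 × 0.5 = 0.15, or 15 points. This is expected in both arms and cancels in the contrast.
- Standard error of the baseline difference: sqrt(2 × 0.3 × 0.7 / 30) = 0.118, or 11.8 points.
- Carried into month 3 by an imbalance of one standard error: 0.118 × 0.5 = 0.059, or about 6 points.
- Standard error of the month-3 difference itself: at a rate of 15%, sqrt(2 × 0.15 × 0.85 / 30) = 0.092; at 30%, 0.118. That is about 9 to 12 points.

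The 6 points are thus 0.059/0.118 = 0.50 to 0.059/0.092 = 0.64 of a standard error. These formulas ignore clustering by physician.

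If side effects were summarised as a score, adjusting for a baseline value with correlation r would cut the variance by r²: 9% at r = 0.3, 25% at r = 0.5 and 49% at r = 0.7. The article describes no such score, so this is a general result and not a property of the trial.

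**The case against.** The strongest reply is that this item carries little weight. Side effects are neither a primary nor a secondary outcome. The sample size is justified by precision, and the protocol itself calls its mediation analyses insufficiently powered and its moderator analyses perhaps underpowered. The one analysis section that names side effects lists them with other problems encountered. For that purpose current prevalence is what matters, since a long-standing side effect can stop a patient taking tablets as readily as a new one. Patients with a modified Rankin score of 3 or more are excluded, which limits residual stroke deficits. Adverse events, in the same cell, have no baseline count by nature. All of this stands, and it sets the size of the point.

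A reader might go further and infer that stroke symptoms and earlier drug effects will be counted as trial side effects, or that a safety comparison between arms will be biased. The documents do not support either. They state no counting or attribution rule and set out no safety comparison. Pre-existing symptoms are expected in both arms, and a chance difference is largely covered by the planned confidence interval. Nor is it right that nothing is recorded before month 3, because the same cell allows for events as reported.

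The reply does not remove the mismatch between the role that Table 1 gives to side effects and the times at which it measures them. With four physicians, balance at entry is not assured, and without a baseline value it cannot be examined.

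**Conclusion.** The point holds as a minor one. Symptoms present at entry cannot be separated from new side effects, baseline balance cannot be checked or adjusted for, and the variable cannot do the pre-intervention moderator's job or show change as a mediator. Only exploratory and descriptive results are affected. The blood pressure analysis is unchanged, as are recruitment, dropout, protocol adherence and satisfaction.

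The conclusion rests on reading Table 1 as the complete schedule and on patients probably being on medication at entry, which the article implies but does not state. That side effects fall within the planned between-group estimates of moderator and mediator measures follows only from the heading they sit under in Table 1. The 6-point illustration depends wholly on the assumed 30% and one-half.

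**What to change.** In Table 1, split the row and add baseline to the time points for side effects, leaving adverse events as they are. Ask the same side-effect questions in the questionnaire session already held at recruitment. In the exploratory between-group estimate, report symptoms that are new or worse since baseline, or adjust for the baseline value. Current prevalence can still be tabulated as a problem encountered.

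The cost is a few extra minutes per patient and one table entry, with no added visit, staff or sample size. It has to be done before enrolment starts, because a baseline value cannot be recovered later.

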After completion of the 3-month trial, patients will return the BP monitors (and smartphones). Those who experience delayed monthly refill (more than 3 days from the designated time) or uncontrolled BP or a missed appointment on two occasions at the standard 3-month clinic visit will be called by the nurse navigator. The nurse navigator will be trained to conduct motivational interviewing to help these patients identify barriers/issues and develop an action plan. This may include a patient restarting some PINGS’ components (e.g., medication intake reminder alert via SMS delivery system reactivation, motivational messages), being referred for additional help (e.g., mental health), and so forth.

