#### Primary outcome measures

For these measures, generalized linear mixed models (GLMM) will be used to compare the two groups with group as primary independent variable and percent success reaching BP control (or resting BP changes individually) as the primary dependent variable (Table 2) [64]. GLMM allow for missing data, measurement at different times and take into account the effect of clustering, i.e., correlation of repeated measurements within patients clustered within MD (Medical Doctor) provider. Group and time (baseline, 3, 6 and 9 months) will be fixed effects; demographics and secondary outcome measures (e.g., medication adherence via the MPR) will be adjustment covariates. We will assess changes over time via a time-by-intervention interaction term in multivariable models. We will estimate differences (for means or proportions) in ancillary moderator and mediator measures between the two groups via 95 % CIs as appropriate (e.g., self-efficacy, autonomous regulation, and so forth.). We will estimate differences (via 95 % CI) in proportions and average slopes between intervention versus control groups and evaluate linearity of trajectories as input for future RCT analysis strategy. We will estimate percent success reaching BP control for each subject over the trial (baseline, 3, 6 and 9 months), and the within-subject longitudinal trajectories (e.g., slopes), and then summarize as mean longitudinal trajectory within each treatment group (e.g., mean slopes with 95 % CI). Intracluster correlation coefficient (ICC) and variance estimates will be obtained of efficacy outcomes and covariance structure of the longitudinal scores for determination of sample size (and hence adequate power) for a future RCT. Multiple imputation methods will be used for missing end-of-study outcomes. Dropout rate, both selective and differential, is an important issue. If more than 10 % of data are missing, we will add an intermediate evaluation point in a future RCT to provide more data for use in endpoint imputation.

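### Side effects and adverse events reach the data partly by a route that is more open to intervention patients, so any pooled between-arm comparison may overstate them under PINGS

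*Protocol article*

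**What the plan says.** In Table 1 (Follow-up phase), side effects and adverse events appear as medication adherence factors in the block of potential moderators and mediators. The time points given are "As reported, and 3, 6, 9 months". No restriction to one arm is stated.

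Under Statistical analyses, Primary outcome measures, the plan reads: "We will estimate differences (for means or proportions) in ancillary moderator and mediator measures between the two groups". This is to be done with 95% confidence intervals where suitable. The Feasibility outcomes paragraph lists medication side effects among problems to be described by frequency distributions, and it ends with general tests between the arms.

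Personal contact differs by arm. For intervention patients, average readings that are too high trigger a call: "the PINGS nurse navigator will call the patient and conduct the BP protocol again, and initiate a follow-up action as needed" (Provider level). The same section adds: "The nurse navigator will also contact those patients who show medication adherence below .80", or whose possession ratio disagrees with self-report. Motivational interviewing on barriers to adherence is to be used. A paragraph under Patient level provides further nurse calls after month 3, for late refills, uncontrolled BP or missed appointments. The control section describes lifestyle messages only, which avoid medication adherence, hypertension and stroke.

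Other contact is shared: "Subjects in both arms of the study will be followed up for 6 months after the initial 3-month trial", with monthly clinic visits in that period.

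**The concern.** One variable is fed by two routes, and nothing in the article separates them. The scheduled route treats the arms alike. The ad hoc route depends on how often someone speaks to the patient, and a nurse who telephones about high readings or poor adherence is described only for the intervention.

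Side effects are an obvious barrier to adherence, and Table 1 itself classes them as an adherence factor, so a call about barriers is a natural occasion for one to be mentioned. A control patient with the same complaint may have no comparable occasion until month 3.

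If all reports are then counted together and compared, unequal opportunity to report could appear as a difference in tolerability. The same unequal capture would distort exploratory work that treats side effects as a moderator or mediator. The Table 1 row is the only adverse-event collection that the article describes.

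**Working it through.** The article gives no adverse-event rate and no capture rate, so there is no figure to reproduce. The size can only be illustrated under assumptions.

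**Inputs.** From Proposed sample size: 2 clusters of 15 = 30 patients per arm. Assumed: the same true risk *p* in both arms (20% to 60%); capture *s* by the scheduled assessments in both arms (50% to 100%); and a fraction *e* of the missed events recovered through nurse calls in the intervention arm only (0 to 100%). *e* is an average over the whole arm, so patients who are never called pull it down.

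**Formulas.**
- Recorded control rate = *p* × *s*
- Recorded intervention rate = *p* × [*s* + (1 − *s*) × *e*]
- Spurious difference = *p* × (1 − *s*) × *e*
- 95% half-width = 1.96 × √[p₁(1 − p₁)/30 + p₂(1 − p₂)/30], ignoring clustering

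**One case in full.** With *p* = 0.40, *s* = 0.70 and *e* = 0.50:
- control 0.40 × 0.70 = 0.28
- intervention 0.40 × (0.70 + 0.30 × 0.50) = 0.40 × 0.85 = 0.34
- difference 6 points, ratio 0.34/0.28 = 1.21
- half-width 1.96 × √(0.34 × 0.66/30 + 0.28 × 0.72/30) ≈ 23.4 points

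**Range at *p* = 40%.** The last column is the chance of a significant excess in the intervention arm when the true risks are equal (nominal 2.5%).

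| *s* | *e* | Control | Intervention | Difference (points) | Ratio | 95% half-width (points) | Chance of significant excess |
|---|---|---|---|---|---|---|---|
| 100% | any | 40% | 40% | 0 | 1.00 | 24.8 | 2.5% |
| 90% | 50% | 36% | 38% | 2 | 1.06 | 24.4 | 3.6% |
| 70% | 50% | 28% | 34% | 6 | 1.21 | 23.4 | 7.2% |
| 50% | 50% | 20% | 30% | 10 | 1.50 | 21.8 | 14.2% |
| 50% | 100% | 20% | 40% | 20 | 2.00 | 22.6 | 39.1% |

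Over all scenarios tried, the spurious difference runs from 0 to 30 points and the half-width from about 15 to 25. The difference exceeds the half-width only in the extreme corner (*p* = 60%, *s* = 50%, *e* = 100%: 30 against 24 points).

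**After the change.** If only scheduled assessments enter the comparison, *e* = 0 and the expected difference is 0 for every *p* and *s*.

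**The case against.** Four objections deserve weight.

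- **Nothing says that the calls elicit or record adverse events.** They are described as repeating the BP measurement, follow-up action and work on adherence barriers. This stands, and it is why the bias is possible rather than established.
- **A between-arm comparison of adverse events is inferred.** The moderator and mediator sentence is qualified, and its examples are psychological constructs. Side effects are named only for description, and no safety endpoint or hypothesis is stated. This also stands, although the inference follows the article's own classification in Table 1.
- **The interval at 30 per arm is nearly always wider than the bias.** That is true, but a confidence interval does not cover systematic error, and the same collection method in a larger trial would keep the bias while the interval narrowed.
- **Forms and question wording belong in the full protocol.** Agreed. The point rests only on the stated schedule taken together with the stated unequal contact.

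A reader might infer three stronger things that the documents do not support.

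- **That PINGS will look less safe for ascertainment reasons alone.** The bias may be nil, and an intervention meant to raise medication intake could produce a genuine difference.
- **That any home BP session can trigger a call.** Readings every 3 days, morning and evening, give 90/3 × 2 = 60 sessions in three months. The trigger is mean BP above threshold, so these are measurement occasions, not contacts.
- **That the monthly visits between months 3, 6 and 9 are missed collection points.** The article says: "During the follow-up period, subjects will attend clinics monthly where their physicians will assess them clinically". A complaint raised there already counts as reported, and the visits apply to both arms.

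**Conclusion.** The concern holds in a limited form. The ad hoc part of adverse-event collection offers unequal opportunity by arm, so a comparison that pools it with the scheduled part may overstate side effects under PINGS. The asymmetry is clearest in months 0 to 3. It may continue afterwards through the later nurse calls, but the control section says that intervention tactics cease at month 3 and both arms then attend monthly.

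The size cannot be fixed from the documents. In the moderate cases at 40% true risk it is 2 to 6 points, with nil as the lower bound. These figures rest on assumed capture rates, on nurse calls bringing events to record, and on the arms being compared at all. The article ties the larger trial to feasibility and preliminary effect, not to an adverse-event criterion. For a feasibility pilot the severity is minor.

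**What to change.** In Table 1 and the analysis text:

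1. Record the source of each side effect or adverse event: scheduled assessment, nurse call or spontaneous report.
2. Base any between-arm estimate only on events elicited with the same questions in both arms at months 3, 6 and 9, preferably by the research assistants whom the Blinding section keeps unaware of group.
3. List nurse-call and spontaneous events by arm, without a comparative estimate.

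The cost is one data field and a sentence in the analysis section, at visits that already take place. The downside is that some events leave the comparative estimate, though they are still listed. The remedy is not perfect, because calls during months 0 to 3 could prime what intervention patients recall at month 3. The source field must be in place before data collection, since it cannot be reconstructed afterwards.
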